### **3.1.4 Study design, methodology, study plan**

Persons aged 65 years and older will be recruited in the two selected districts of Nakhon Phanom Province and followed weekly for one year to identify any new episodes of ARI or SARI. Baseline information will be collected from all participants, including functional status and frailty indicators, chronic diseases, smoking history, and variables related to socioeconomic status. Participants will be asked how far the closest health center is from them and household latitude and longitude will be collected in order to calculate distances to medical facilities. ARI will be defined as a new onset of cough or worsening of chronic cough, with or without fever.

SARI will be defined as new onset of cough, worsening of chronic cough or difficulty breathing with a fever  $\geq 38^{\circ}$  Celsius that requires hospitalization. Nasal and nasopharyngeal samples taken from persons with ARI or SARI will be tested using real-time reverse-transcription polymerase chain reaction (rRT-PCR) for influenza and respiratory syncytial viruses. The incidence of laboratory-confirmed, influenza-associated ARI and SARI will be compared between vaccinated and unvaccinated cohort participants, controlling for baseline functional status and underlying medical conditions that might confound the primary association. Data on costs of visits for ARI and SARI for pneumonia or acute respiratory illness will be collected, along with information on the costs of the vaccination campaign, to determine the cost per influenza episode averted and the value for money of the immunization campaign. Results will assist the Thai Ministry of Public Health to make informed decisions related to improving vaccination coverage among the elderly in Thailand.

In addition to vaccine effectiveness and cost effectiveness data, this study will also take the opportunity to measure the effect of ARI and SARI on functional status among the elderly, measure the incidence of influenza-associated COPD exacerbations among those with ARI or SARI, evaluate humoral immune response of IIV3 through measurement of hemagglutination inhibition assay (HAI), and measure the incidence of respiratory syncytial virus (RSV) among the elderly with ARI or SARI.

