All participants will be provided a self-swabbing kit from the study team that includes Dacron swabs and test tubes with transport media (TM) which are already labeled with the participants' hospital number, along with written instructions. Participants will be asked to take one nasal self-swab, and to place it in the refrigerator in a separate test tube filled with 1-3ml of TM. Participants will then be asked to describe the procedure to ensure they understand the full technique and will be guided appropriately. Participants will be given a study card with their study ID number and assigned health volunteer's telephone number. Participants who experience an ARI, defined as new onset of cough or worsening of chronic cough, will be asked to take a self-swab as soon as possible and then to call their assigned health volunteer to make an appointment to have their swab collected and answer some questions for the ARI/SARI Episode Questionnaire at the time of the appointment (which will be within 24 hours). The assigned health volunteer will bring an ice box and new Dacron self-swab kit to the sick participant's home, and the specimen will be transported in the ice box by the health volunteer to the sub-district health center for temporary storage. Health volunteers will also conduct the Functional Status Questionnaire three to four weeks after the onset of a participant's ARI or SARI and the Outcomes and Costs of ARI Questionnaire 1 week after the participant recovers which will be monitored through the weekly calls and by the study team. If a participant is very ill due to an ARI and needs assistance in taking a nasal self-swab, they can ask their assigned health volunteer for help in obtaining the specimen. Health volunteers will also be trained to contact their assigned participants weekly to identify ARI events that they have not been notified of already and to take a weekly questionnaire. They will attempt three contacts, by phone or in person, at different times of the day before considering the participant to have missed the week. In the case of an ARI event, participants who have not yet taken a self-swab will be asked to self-swab immediately.

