| 3                                                                                                                                                                                                                           | In the last week, have you been sick with a new, acute illness?        | 1 Yes
2 No
77 Do not know                                                                                        | If no, skip to end of questionnaire |
| In the last week, have you had a NEW:                                                                                                                                                                                       |                                                                        |                                                                                                                        |                                            |
| 4                                                                                                                                                                                                                           | Cough, or a worsening of a chronic cough?                              | 1 Yes
2 No
77 Do not know                                                                                        |                                            |
| 5                                                                                                                                                                                                                           | Fever?                                                                 | 1 Yes
2 No
77 Do not know                                                                                        |                                            |
| 6                                                                                                                                                                                                                           | Nasal discharge/congestion?                                            | 1 Yes
2 No                                                                                                          |                                            |

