|                                                                                                                                                                                                                                              |                                                          |                                 |  |
|----------------------------------------------------------------------------------------------------------------------------------------------------------------------------------------------------------------------------------------------|----------------------------------------------------------|---------------------------------|--|
|                                                                                                                                                                                                                                              |                                                          | 77 Do not know                  |  |
| 7                                                                                                                                                                                                                                            | Sore throat?                                             | 1 Yes
2 No
77 Do not know |  |
| 
If no report of a new cough or worsening of a chronic cough, please thank patient for their time and let them know that they do not need to take nasal self-swabs this week. Go to end of survey.
                              |                                                          |                                 |  |
| 8                                                                                                                                                                                                                                            | Did you already collect nasal swabs for the new illness? | 1 Yes
2 No
77 Do not know |  |
|                                                                                                                                                                                                                                              |                                                          |                                 |  |

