|                                                                                                                                                                     |                                          |                                                                                                                        |  |
|---------------------------------------------------------------------------------------------------------------------------------------------------------------------|------------------------------------------|------------------------------------------------------------------------------------------------------------------------|--|
|                                                                                                                                                                     |                                          | 77 Do not know                                                                                                         |  |
| If participant answered no for question 2, tell patient they do not need to take nasal swabs at this time and thank them. Go to end of Questionnaire. |                                          |                                                                                                                        |  |
| 6                                                                                                                                                                   | When did this illness begin?             | 1 Today
2 Yesterday
3 2 days ago
4 3 days ago
5 4 days ago
6 5 days ago
7 6 days ago
8 7 days ago |  |
| 7                                                                                                                                                                   | At what time did the illness begin?      | _____                                                                                                                  |  |
| 8                                                                                                                                                                   | What day was the nasal self-swab taken   | MM/DD/YY                                                                                                               |  |

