**For the study team in the Community:**

1. Show a video demonstrating the above technique to the participant step-by-step without the materials which follow the below written instructions “How to take a nasal self-swab”
2. Ask the participant to demonstrate the technique for taking a nasal self-swab without the materials to show that they understand the technique
3. Instruct the participant to take a nasal self-swab when they have a new onset of cough or worsening of chronic cough
4. Instruct the patient to store their nasal swab test tube in the refrigerator
5. Then instruct patient to immediately call their assigned health volunteer to schedule a time for the swab to be picked-up within 24 hours
6. Write health volunteer’s telephone number for the patient on the written instruction sheet and let participant know that they can call the health volunteer if they have any concerns or need help.
7. Ask patient to verbally repeat steps 3 to 5 to demonstrate understanding

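### Form 4c releases participants who are newly ill without cough from self-swabbing 'this week', which conflicts with the rule to swab as soon as cough starts

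*Protocol*

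**What the plan says.** The case definition is cough-based. Section 3.1.4 states: "ARI will be defined as a new onset of cough or worsening of chronic cough, with or without fever".

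The rule on when to swab appears twice and does not depend on the weekly call. In section 7.5.1, participants who experience an ARI "will be asked to take a self-swab as soon as possible and then to call their assigned health volunteer". Appendix 5a tells the study team: "Instruct the participant to take a nasal self-swab when they have a new onset of cough or worsening of chronic cough".

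Form 4c, the weekly contact script, works as follows. Item 3 asks about a new acute illness in the last week, with the skip "If no, skip to end of questionnaire". Those who pass item 3 are asked about cough, fever, nasal discharge and sore throat under the stem "In the last week, have you had a NEW". The instruction that follows begins "If no report of a new cough or worsening of a chronic cough, please thank patient for their time" and continues that the volunteer should "let them know that they do not need to take nasal self-swabs this week". The survey then ends.

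Form 4d, the episode form completed by the same volunteers, treats the no-cough answer differently: "tell patient they do not need to take nasal swabs at this time and thank them".

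**The concern.** The item 3 skip determines who hears the 4c message. Participants with no new illness leave the form before reaching it. It is read only to people who have just reported a new acute illness, or do not know whether they have one, and who have no cough at the time of the call. They may already have fever, nasal discharge or sore throat. If a cough follows a day or two later, the same illness becomes an ARI that the protocol wants swabbed at once, yet the volunteer's latest instruction was that no swab is needed this week.

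Laboratory-confirmed influenza-associated ARI and SARI is the outcome of primary objective 1.1, so timely swabbing is what turns an illness into a countable event. The Limitations section already lists forgetting to self-swab as a weakness. A scripted release from swabbing adds to it.

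**Working it through.** The protocol gives no figure on this point, so the check is a comparison of the instructions, followed by the timing that the weekly cycle implies.

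**1. The instructions for a participant with a new illness, no cough at the call, and a cough that starts afterwards**

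| Place | Instruction | Covers a cough that starts after the call? |
|---|---|---|
| Section 7.5.1 | Self-swab as soon as possible at ARI onset, then call the volunteer | Yes: swab |
| Appendix 5a | Self-swab at new or worsening cough | Yes: swab |
| Form 4d | No swab needed 'at this time' | No: limited to the moment of the report |
| Form 4c | No swab needed 'this week'; end of survey | Yes, if read forward: no swab |

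The first two rows and the last give opposite answers for the same person on the same day. Form 4d avoids the conflict by its choice of words.

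**2. The delay if the 4c message is followed**

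Let the cough start *d* days after the call, with *d* between 0 and 7. The next scheduled prompt comes 7 − *d* days after cough onset:

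- *d* = 1: 7 − 1 = 6 days
- *d* = 2: 7 − 2 = 5 days
- *d* close to 0: about 7 days, the maximum

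At that contact, section 7.5.1 has anyone who has not yet swabbed do so immediately, and form 4c arranges collection. The specimen is therefore late but normally still obtained.

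**3. If the next contact is missed**

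Section 7.5.1 lets a week count as missed after three failed attempts. The delay then becomes 14 − *d* days; for *d* = 1 this is 13 days. Form 4c looks back one week only, and the onset codes in form 4d stop at 7 days ago, so a cough that began before that window may not be recorded as new. This is how an event could be missed rather than tested late.

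**4. What cannot be calculated**

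The number of events affected depends on how often influenza illness begins without cough, how long the cough lags, how many participants would let the message override their training, and how PCR yield falls with delay. The protocol gives none of these.

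**The case against.** The strongest defence is that 'this week' closes the week under review. Form 4c is a per-week record, its header carries the week of follow-up, and its symptom items look back over the last week. On that reading the message says only that no specimen is due for this contact, and forms 4c and 4d agree. The reading is possible, but the form does not state it, and telling someone what they need not take points more naturally to the days ahead. Form 4d shows that unambiguous wording was available.

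The second defence is that the standing rule is never revoked and there are backstops. Appendix 5a has participants repeat the swab-and-call steps aloud. They hold a kit, written instructions and the volunteer's number. The next weekly contact asks about cough and prompts a swab. Nurses take nasopharyngeal swabs at health centres and hospitals for cough or difficulty breathing, so severe illness does not depend on form 4c. All of this stands. It makes delay, not loss, the main effect, but it does not reconcile two opposite instructions.

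A reader might go further and infer a loss of power or an inflated vaccine effectiveness. The protocol does not support either:

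- *Power.* With 1,362 per group and one-year risks of 6% and 3.6% (the stated 40% effectiveness, taking 6% as the unvaccinated risk), expected events are 1,362 × 0.06 + 1,362 × 0.036 = 130.8. Assume, without any source here, that 20–40% of influenza ARIs begin 1–2 days before cough and that calls fall at random. The share whose call lands in that window is 0.2 × 1/7 = 2.9% to 0.4 × 2/7 = 11.4%, or 3.7 to 14.9 events. Continuity-corrected power would fall from 81.1% to 79.8% at the lower end and 75.7% at the upper end, but only if every such event were lost, which the backstops contradict. Over two years, treated as 12% against 7.2%, the upper-end fall is from about 99% to about 97.5%.
- *Bias.* If 10% of vaccinated and 5% of unvaccinated events were lost, a true 40% would read 1 − 0.6 × 0.90/0.95 = 43.2%. This needs vaccinated illness to begin without cough more often, and nothing in the protocol says that it does.

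**Conclusion.** The wording conflict is real and concerns the operative weekly script for a primary outcome. Read in its natural, forward sense, form 4c releases a newly ill participant from the self-swab that section 7.5.1 and Appendix 5a require at cough onset, and it is broader than form 4d for the same answer.

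The demonstrable consequence is a swab prompted up to about 7 days after cough onset instead of as soon as possible, and later or occasionally not at all when the next contact is missed. This rests on two assumptions: that the participant takes the phrase to cover the coming days, and that they follow it over their enrolment training. How many events are affected cannot be derived from the protocol. The power and effectiveness figures above are illustrations on unsupported inputs and should not be quoted as findings.

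The point is modest in expected impact, but it is worth correcting because it bears on when primary-outcome specimens are taken and the correction is nearly free.

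**What to change.** In the instruction after item 7 of form 4c, replace 'this week' with form 4d's 'at this time'. Add the protocol's own standing rule, for example: no nasal self-swab is needed at this time; if a new or worsening cough starts before the next contact, take a self-swab as soon as possible and call your volunteer.

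The same closing reminder could be added to the no-cough exit of form 4d so that the two volunteer forms match.

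The cost is one sentence on the electronic form and in volunteer training. No visits, staff, specimens beyond those already required, or analyses are added.

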**END OF QUESTIONNAIRE**

**4d. ARI/SARI episode Questionnaire (For Health Volunteers)**

|                                       |                                                                 |                                 |             |
|---------------------------------------|-----------------------------------------------------------------|---------------------------------|-------------|
| Study identification number of caller |                                                                 |                                 |             |
| Health Volunteer's name               |                                                                 |                                 |             |
| Date                                  | (DD/MM/YY)                                                      |                                 |             |
| Thank you for notifying me.    |                                                                 |                                 |             |
| No.                            | Questions and filters (variable names)                   | Coding categories        | Skip |
| 1                                     | In the last week, have you been sick with a new, acute illness? | 1 Yes
2 No
77 Do not know |             |
|                                       |                                                                 |                                 |             |
| In the last week, have you had a NEW: |                                                                 |                                 |             |
| 2                                     | Cough, or a worsening of a chronic cough?                       | 1 Yes
2 No
77 Do not know |             |
| 3                                     | Fever?                                                          | 1 Yes
2 No
77 Do not know |             |
| 4                                     | Nasal discharge/congestion?                                     | 1 Yes
2 No
77 Do not know |             |
| 5                                     | Sore throat?                                                    | 1 Yes
2 No                   |             |

|                                                                                                                                                                     |                                          |                                                                                                                        |  |
|---------------------------------------------------------------------------------------------------------------------------------------------------------------------|------------------------------------------|------------------------------------------------------------------------------------------------------------------------|--|
|                                                                                                                                                                     |                                          | 77 Do not know                                                                                                         |  |
| If participant answered no for question 2, tell patient they do not need to take nasal swabs at this time and thank them. Go to end of Questionnaire. |                                          |                                                                                                                        |  |
| 6                                                                                                                                                                   | When did this illness begin?             | 1 Today
2 Yesterday
3 2 days ago
4 3 days ago
5 4 days ago
6 5 days ago
7 6 days ago
8 7 days ago |  |
| 7                                                                                                                                                                   | At what time did the illness begin?      | _____                                                                                                                  |  |
| 8                                                                                                                                                                   | What day was the nasal self-swab taken   | MM/DD/YY                                                                                                               |  |
| 9                                                                                                                                                                   | What time was the nasal self- swab taken | _____                                                                                                                  |  |
|                                                                                                                                                                     |                                          |                                                                                                                        |  |
| Collect a nasal self-swab and take to assigned health center.                                                                                         |                                          |                                                                                                                        |  |

